**Figure 2 figure2:**
[figure not shown]
Illustration of the cardiopulmonary exercise test (CPET) protocols. The CPET protocol includes 2-minute stages starting at 25 W with load increments of 10 or 20 W per stage. Venous blood samples (filled drops), capillary blood samples (unfilled drops), blood pressure measurements, and rating of perceived exertion assessments are indicated.

Absolute and relative termination criteria [54,57].
**Absolute termination criteria**
Decrease in systolic blood pressure of >10 mm Hg compared to the initial blood pressure despite an increase in stress with other signs of ischemiaDefinite angina pectorisIncreasing cerebral symptoms (eg, ataxia, confusion, or presyncope)Signs of reduced peripheral perfusion (cyanosis or pallor)Technical reasons that make it impossible to adequately analyze the electrocardiogram or systolic blood pressureThe study participant’s desire to terminate the exercisePersistent ventricular tachycardiaST segment elevation of at least 0.1 mV in leads without pathological Q waves (not augmented vector right or precordial lead V1)
**Relative termination criteria**
Decrease in systolic blood pressure of >10 mm Hg compared to the initial blood pressure despite an increase in stress without other signs of ischemiaIncreasing angina pectorisArrhythmias other than sustained ventricular tachycardia, including multifocal ventricular extrasystoles, triplets, supraventricular tachycardia, blockages, or atrial fibrillationFatigue, breathlessness, wheezing, leg cramps, or claudicationDevelopment of a bundle branch block or intraventricular conduction delay that cannot be distinguished from ventricular tachycardiaReduced cadence of <40 revolutions per minuteArterial hypertension (250 mm Hg systolic or 115 mm Hg diastolic)ST segment or QRS complex changes, such as horizontal or descending ST segment depression (>0.2 mV) or pronounced change in position type

##### Lactate Diagnostics

For lactate diagnostics, capillary blood samples (20 μL) are taken from the earlobe 5 minutes before, during, and at the end of each exercise stage (last 30 seconds) and 3 minutes after completion of the CPET. Blood samples are measured immediately after the CPET through the polarographic determination method using an EKF Biosen S-Line measuring device (EKF Diagnostics GmbH) and analyzed using the winlactat 4.0 software (mesics GmbH). Lactate diagnostics include the measurement of the lactate concentration (mmol/L) and the determination of individual aerobic and anerobic thresholds for each participant using the *baseline +1.5 mmol/L method* according to Dickhuth et al [61].

##### cfDNA Diagnostics

At T0, venous blood samples are taken from the antecubital vein 5 minutes before, immediately after, 30 minutes after, and 60 minutes after the CPET using 4.9 mL of K3-EDTA Monovette (Sarstedt). In contrast to those at T0, the blood samples are only taken before and after the CPET at T1 and T2. The samples are centrifuged at 2500 × g for 15 minutes at room temperature. In total, 2 mL of plasma are taken and centrifuged a second time at 2500 × g for 15 minutes at room temperature. Plasma aliquots (150 and 550 µL) are collected in 1.5-mL tubes and stored at −20 °C according to established guidelines [62].

Concentrations of cfDNA will be measured using quantitative real-time polymerase chain reaction with unpurified plasma, as described previously [63]. The pipetting steps will be conducted using an automated pipetting system (ASSIST PLUS; INTEGRA Biosciences GmbH).

#### Muscle Strength Testing

HGS will be quantified during participants’ clinical assessments (before and after the CPET) by medical assistants using a Jamar hydraulic hand dynamometer (SH5001; Saehan Industries GmbH) following an established protocol by Nacul et al [64]. Participants are instructed to sit in an upright position and squeeze the handgrip as hard as possible, lasting 3 seconds, in 3 consecutive trials with 30 seconds of rest between trials. The entire procedure takes approximately 3 minutes to complete, including instructions. To examine changes in HGS over the course of the study, HGS_max_ is defined as the highest value of the 3 consecutive trials. In addition, we calculate the HGS_diff_ to determine the decrease in HGS between the 3 consecutive trials by subtracting the mean value between the second and third trials from the value of the first HGS trial, as described elsewhere [64].

#### Digital Infrastructure

The digital infrastructure that will be used during the intervention phase is divided into 2 different parts. The first part is a central website designed for mobile and desktop use (WordPress; WordPress Foundation). The second part is the software Mattermost (mobile app and desktop application; Mattermost Inc), which is used for digital communication between therapists and patients (Figure 3).

The website consists of three main areas: (1) a diary for monitoring and controlling clinical condition and training load in addition to the questionnaires already described in the *Questionnaires* section; (2) an education area with short educational videos about PCC and exercise and respiratory therapy, including a detailed explanation and the pacing approach; and (3) a therapy program area including written materials (eg, weekly therapy plans, instructions for each type of training, and control of training intensity depending on the clinical condition).

All important information on the use of the website and Mattermost is provided in the study manual and communicated to the participants via email. In the intervention phase, the IG participants can use both the website and Mattermost. In contrast, CG participants can use only a restricted version of the website (without the education or therapy program areas) for daily reporting via the clinical condition and training load diary (CCTD).

**Figure 3 figure3:**
[figure not shown]
Digital infrastructure—(A) website for mobile and desktop use (WordPress; WordPress Foundation) and (B) mobile app and desktop application (Mattermost; Mattermost Inc). The author consents to the use of their image in this publication.

#### IG Setup

On the basis of the CPET results and the algorithm listed in Table 2, IG participants are assigned to 1 of 3 TGs (TGs 1-3). Before the start of the intervention, all participants will take part in 2 video-based introductory sessions in the first week to get to know their personal sports therapist, learn how to use the digital infrastructure, and understand the therapy program (eg, therapy plan and monitoring of clinical condition).

**Figure 4 figure4:**
[figure not shown]
Exemplary weekly therapy plan for training group 3. The intervention and follow-up phases during the 16-week period are divided into 2 mesocycles (8 weeks) and 16 microcycles (1 week). The therapy plan consists of a combination of exercise and respiratory training types, training days, and recovery days. Participants are required to keep a daily clinical condition and training load diary (CCTD).

The 3 TGs (Figure 1) follow an individual therapy plan. For TG 1 participants, the therapy plan includes respiratory and POTS training every day for at least 5 times a week. Respiratory training is based on the apnea training method [65] for increasing hypoxemia and ischemia tolerance. One respiratory training session consists of 3 sets of 4 repetitions, with a 2- to 3-minute pause between sets. One repetition consists of a deep inspiration maneuver followed by 4 maximum expirations and 4 submaximal inspirations to the level of resting inspiration. A POTS training session involves position change exercises for the arms, legs, and total body (eg, an exercise for standing up). The structure of each exercise consists of 2 to 3 sets with 5 to 10 repetitions, with a 1-minute pause between sets and 2 to 3 minutes between each exercise. For TG 2 and TG 3 participants, the therapy plan includes exercise training every other day but at least 3 times a week. TG 2 engages in endurance training as a substitute for POTS training. Moreover, TG3 performs both endurance and strength training instead of POTS training. Endurance training, designed as aerobic interval training and patient-centered training (eg, walking and cycling), entails 1 to 2 sets for TG 2 and 2 to 3 sets for TG 3, with a set pause of 2 to 3 minutes. Each set involves 8 to 10 repetitions with a work-to-rest ratio of 30:30 seconds or 30:60 seconds, with intensity control based on the modified Borg scale (0-10) for the RPE. Work intervals aim for an intensity between 4 and 6 (less strenuous to moderately strenuous), whereas (active) rest intervals target an intensity between 1 and 3 (very light to light). The individual progression or regression of the training load (eg, number of sets, intensity, and active or passive rest) depends on the patient’s exercise tolerance and can be carried out in consultation with a personal sports therapist.

All participants, both from the IG and CG, will be asked not only to practice additional pacing in their daily lives to be active but also to use their energy resources as efficiently as possible. To this end, based on the Royal College of Occupational Therapists pace, plan, and prioritize principle pacing approach [66] and the CPET, we developed a new objective pacing approach based on PO at the individual anaerobic threshold—ventilatory threshold 2/lactate threshold 2 (VT2/LT2)—as the threshold for continuous physical capacity and the metabolic equivalent of task (Figure 5 [67]) [67,68].

#### Monitoring of Clinical Condition and Control of Training Load

The daily recording of the clinical condition and the interactive adjustment of the exercise therapy aim to reduce or stabilize symptoms and adjust the training load to achieve the best training effects.

The training load is regulated based on clinical condition using a clear algorithm (Figure 6), which includes the assessment of the clinical condition based on the RPSS and the recommendation of the training intensity based on the RPE. The RPSS was developed through our clinical experience with PCC at the sports medicine outpatient clinic, Mainz [69], and through insights from international literature on symptom occurrence in PCC [7,12]. The successful application of the RPSS in practice constitutes its inaugural use in a scientific context. Both the RPSS and RPE will be documented in the CCTD. The RPSS comprises the following items: fatigue (influenza-like symptoms or general fatigue), dyspnea (breathing difficulties, headache, visual disturbance, or chest pain), POTS (high pulse, inability to stand, and need to lie down), anxiety (anxiety, panic, or avoidance), and hypersensitivity (to noise, light, temperature, touch, and muscle or nerve pain). Each symptom group is accompanied by a free-text field for individual comments that is rated on a scale from 0 to 10 (0=no symptoms; 1-3=mild symptoms; 4-6=moderate symptoms; 7-10=severe to maximum symptoms).

Participants are asked to complete the RPSS every day in the morning to monitor their clinical condition. Every day starting with even 1 symptom cluster between 7 and 10 (PEM condition) is counted as a PEM episode. On training days, the RPSS should be completed by the start of training at the latest. To avoid exercise-induced overload and exacerbation of clinical symptoms, patients should only exercise when each symptom cluster has a value of ≤6 (Figure 6). Ideally, each symptom cluster should have a value between 0 and 3 (good clinical condition); then, patients can train with an RPE of 4 to 6 to maintain good clinical condition and provide an effective training stimulus. Even if only 1 symptom cluster has a value between 4 and 6 (pre-PEM condition), the RPE value must be set to 1 to 3 during training. However, if any of the RPSS symptom clusters have a value between 7 and 10 (PEM condition), the upcoming exercise training session should be canceled. In addition, if symptoms increase by ≥7 values during training, the current training session should be stopped. Finally, an increase in symptoms of ≥2 values in more than one symptom cluster should also be considered for training load management. The possible cause for this increase should be investigated via teleconsultation. After the training session or at the end of the day at the latest, participants are required to document their training (type; duration; intensity; and, if applicable, commentary) in the CCTD.

**Figure 6 figure6:**
[figure not shown]
Clinical condition is assessed based on symptom severity (rating scale for perceived symptom severity), and training recommendations (rating of perceived exertion [RPE]) are derived accordingly. If any symptom cluster indicates a more severe condition (eg, pre–postexertional malaise [PEM] or PEM condition), the corresponding Borg value is applied. CCTD: clinical condition and training load diary; POTS: postural orthostatic tachycardia syndrome.

#### CG Setup

All the questionnaires, clinical assessments, and CPET scores at each examination time point correspond to the IG. After T0, the CG participants receive an email with written information explaining the importance of self-management of symptoms and activities through the pacing approach. CG participants will be motivated toward a healthy lifestyle (eg, nutrition and stress control) and receive pacing recommendations but will not receive web-based exercise or respiratory therapy or teleconsultations. The term *treatment as usual* refers to clinical assessment, the CPET, a sports medicine consultation on healthy habits, and the pacing approach. After T1, the CG will undergo the same intervention as the IG but in the follow-up phase.

The statistical significance will be set at α<.05. The magnitude of the changes between time points, as well as the magnitude of the differences in changes between the groups, will be assessed using effect sizes. The threshold values for effect sizes will be 0.2 (small), 0.6 (moderate), 1.2 (large), and 2.0 (very large) [72,73]. In addition, 95% CIs for the between-group differences in changes will be estimated, and magnitude-based inferences will be made with reference to the smallest worthwhile change, which is calculated as 0.2 multiplied by the between-subject variation at T0 [73]. Correlations between variables will be assessed using parametric (Pearson) and nonparametric (Spearman rank) tests depending on the distribution of the variables. In the case of multiple comparisons, *P* values will be adjusted using appropriate procedures.

The sample size estimation is based on an a priori power analysis (repeated measures; interaction between group [intervention vs control] and time [before vs after the intervention]) performed using G*Power (version 3.1.9.7). Assuming a power of 0.8 and a medium to large effect (Cohen *f*=0.35) on the VO_2peak_ (in accordance with the work by Bacon et al [74]), 67 participants are needed. Considering the calculated required sample size and a dropout rate of 15% to 20% [53,75], the target number of study participants is set at a total of 80, or 40 participants per group.

Adherence to the intervention is defined as the percentage of training sessions completed of the prescribed training sessions [75]. Participants who drop out of the intervention or complete <60% (ie, <17 of the predefined 24 training sessions for TG 1) of the prescribed training are defined as dropouts. For those in the IG, adherence during the follow-up phase will also be tracked to assess sustained engagement without therapeutic supervision. Adherence to the training requirements will be assessed based on the information provided by the participants via the CCTD. Participants will continue to be monitored after their withdrawal from the study if they agree.

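### Magnitude-based inferences are planned on the same group differences as the 0.05 test, with no rank, no cut-offs and no error control, so a non-significant primary outcome can receive a positive verdict

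*Protocol article*

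**What the plan says.** All of this stands in Methods, Statistical Analysis Plan, of the protocol article.

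- Test: "The statistical significance will be set at α<.05". The primary comparison is IG against CG from T0 to T1, by repeated-measures ANOVA or a linear mixed model, and superiority is attached to that comparison.
- Estimate: "95% CIs for the between-group differences in changes will be estimated", alongside effect sizes.
- Further inference: "magnitude-based inferences will be made with reference to the smallest worthwhile change", "which is calculated as 0.2 multiplied by the between-subject variation at T0".
- Sample size: "Assuming a power of 0.8 and a medium to large effect" on VO2peak (Cohen f of 0.35), "67 participants are needed", raised to 80 for dropout.
- Multiplicity: P values are to be adjusted by a procedure that is not named. Nothing is said about multiplicity for the magnitude-based verdicts.

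The Outcomes section names two primary outcomes, the changes in VO2peak and in VE/VCO2 slope. For the magnitude-based part the article gives no probability cut-offs for benefit or harm and no verdict labels. It does not say how a verdict that disagrees with the test is to be handled.

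**The concern.** Magnitude-based inference turns an estimate and its standard error into a chance that the true difference exceeds the smallest worthwhile change in the good direction, and a chance that it exceeds it in the bad direction. It then attaches a verbal verdict. Positive verdicts can be reached when the 95% CI still includes zero, and their false-positive rate is not fixed at any chosen level.

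The sample size rests on the power of a significance test, and the stated aim is superiority. If VO2peak or VE/VCO2 slope misses significance but is reported as 'possibly beneficial', readers receive a positive statement that the 0.05 level does not protect. With no cut-off fixed in the article, the wording could also be chosen once the data are known.

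This is not detail left to a fuller plan. The article itself commits to the method. Since effect sizes and 95% CIs are already planned separately, what the clause adds is the inference.

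**Working it through.** **Inputs from the article.** Alpha 0.05; power 0.8; f = 0.35; N = 67; target 80 (40 per arm); "a dropout rate of 15% to 20" per cent; smallest worthwhile change 0.2 times the T0 between-subject variation, read here as the SD.

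**Assumed, because the article does not give them.** r from 0.5 to 0.95; verdict cut-offs, shown as a range; a two-sided test; a change-score comparison.

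**1. The plan's own figure.** With noncentrality f²N and 1 and N−2 degrees of freedom, N = 67 gives 0.1225 × 67 = 8.21 and power 0.806; N = 66 gives 0.7997. So 67 is reproduced on this convention. It is the size for a significance test. Completers: 80 × 0.85 = 68, or 34 per arm; 80 × 0.80 = 64, or 32 per arm. I use 34 (66 degrees of freedom).

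**2. Standard error in T0-SD units.** SE = √(2(1−r)) × √(2/34). For r = 0.5, 0.7, 0.8, 0.9 and 0.95 this is 0.243, 0.188, 0.153, 0.108 and 0.077.

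**3. When a verdict is positive.** Orient the sign so that positive is favourable (a lower VE/VCO2 slope counts as positive).
- Chance of benefit above 25%: estimate > 0.2 − 0.678 × SE.
- Chance of harm below 5%: estimate > −0.2 + 1.668 × SE.
- Chance of harm below 0.5%: estimate > −0.2 + 2.652 × SE.

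Both the benefit and the harm condition must hold, so the larger limit decides. At r = 0.7 with harm below 5%, the limits are 0.073 and 0.113. Under no effect, P(estimate > 0.113) = P(Z > 0.113/0.188) = P(Z > 0.60), about 27%.

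**4. Null simulation.** No true effect, 34 per arm, at least 200,000 trials per setting, SE estimated in each trial:

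| Rule (favourable direction) | r 0.5 | r 0.7 | r 0.8 | r 0.9 | r 0.95 |
|---|---|---|---|---|---|
| Significant at 0.05 | 2.5% | 2.5% | 2.5% | 2.5% | 2.5% |
| Benefit >25%, harm <5% | 20% | 27% | 26% | 12% | 2.7% |
| Benefit >25%, harm <0.5% | 4% | 6% | 10% | 12% | 2.7% |
| Benefit >75%, harm <5% ('likely') | 6.7% | 4.1% | 2.4% | 0.6% | <0.1% |
| Benefit >95%, harm <5% | 0.7% | 0.4% | 0.2% | <0.1% | <0.1% |

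For r from 0.5 to 0.9, 32 or 40 per arm gives the same picture (9% to 29% for the second row). Estimating the T0 SD in each trial, rather than fixing it, changes little.

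**5. Two primary outcomes.** Assume a correlation of 0.4 between the outcomes, 34 to 40 per arm and r from 0.5 to 0.9. A false favourable statement on at least one outcome, by a significant test or a verdict, occurs in 17% to 43% of trials with harm below 5%, and in 7% to 20% with harm below 0.5%. The unadjusted test alone gives about 4.6%.

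**6. One illustrative result.** At r = 0.7, an observed difference of 0.15 SD has a 95% CI of 0.15 ± 1.997 × 0.188, or −0.23 to 0.53, and P = 0.43. The chance of benefit is P(t > (0.2 − 0.15)/0.188), about 40%. The chance of harm is P(t < (−0.2 − 0.15)/0.188), about 3%. Under the looser rule this is 'possibly beneficial'.

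**The case against.** The best defence is the order of the text. Superiority is tied to the model comparison, alpha comes first, the power calculation concerns the group-by-time interaction, and the magnitude-based inferences are introduced as an addition. P values and 95% CIs would stand beside any label. The Results section also promises objective reporting whatever the outcome. All of this stands, and it limits what may be concluded.

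Three stronger readings are tempting, and the article does not support them.

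- *That magnitude-based inference is a second decision rule which defeats the superiority test.* Nothing says that a verdict establishes superiority or overrides a non-significant test. The risk lies in how results are stated; the test itself is unchanged.
- *That false claims of benefit will far exceed 5%.* That follows only under some assumed cut-offs and correlations. With harm below 0.5% and r = 0.5 the rate is 4%. The high figures come mostly from counting the weakest label, 'possibly', as a claim of benefit.
- *That positive verdicts go with a 95% CI reaching into harm.* With harm below 0.5% this cannot happen, because the lower 95% limit then lies above −0.2 SD. With harm below 5% it occurs in 38%, 33%, 13% and 0% of positive verdicts at r = 0.5, 0.7, 0.8 and 0.9.

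The defence does not supply a sentence that makes the verdicts descriptive, or a cut-off that bounds their error. The text calls them inferences, on the same differences that are tested.

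**Conclusion.** The point holds in conditional form. The article plans magnitude-based inferences on the differences tested at 0.05, without ranking them below the test, labelling them descriptive or controlling their error. That much is in the text and needs no assumption.

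The size does need assumptions. At 34 per arm with no true effect and r from 0.5 to 0.9, a verdict of at least 'possibly beneficial' appears in about 12% to 27% of trials (harm below 5%) or 4% to 12% (harm below 0.5%), against 2.5% for a significant favourable test. If only 'likely' verdicts count it is at most about 7%, and at r near 0.95 about 3%, so the inflation is then small or absent. The sample size is not affected. The change should be made before results are reported; it is a matter of protecting the primary conclusion and does not mean that the primary test is invalid.

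**What to change.** For the two primary outcomes, delete the magnitude-based inference clause and state three things:

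1. Superiority is decided only by the 0.05 test of the IG-CG difference in T0-T1 change, with the multiplicity adjustment applied.
2. The planned 95% CI is reported with its position relative to zero and to the smallest worthwhile change, as description only.
3. Labels such as 'possibly beneficial' or 'likely beneficial' are not used for these outcomes.

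The cost is one deleted clause and a clarifying sentence. No new data or analysis is needed, because the CI and the smallest worthwhile change are already planned. What is lost is some softer positive wording. The Results section says that analysis is ongoing and nothing has been published, so the change can still be made and dated before reporting.
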